## Research aims and hypothesis

2

In this study, we aim to (1) assess the longitudinal relationship between mushroom consumption and cognitive decline, measured by the absolute change in Mini Mental State Examination (MMSE) scores over a median of 10 years among surviving DaHA participants; (2) test the effects of mushroom powder (two 500 mg capsules per day) on cognitive function measured using the Symbol Digit Modality test (SDMT), the Color Trail Test (CTT) and the Rey Auditory Verbal Learning Test (RAVLT) over 12 months and 24 months, in comparison with controls who consume placebo; (3) examine the underlying protective mechanisms using biomarkers of aging (epigenetic clocks and inflammation) and measuring blood ergothioneine levels; (4) explore epigenome-wide DNA methylation changes following mushroom powder intervention and assess whether such changes correlate with cognitive and biomarker outcomes, without presupposing a beneficial direction. We hypothesized that (1) mushroom consumption will predict slower cognitive decline in a dose-dependent manner over a median 10-year period among DaHA participants; (2) daily mushroom powder consumption over 12 and 24 months will improve cognitive function (processing speed, executive function, memory) among middle-aged and young-old adults; (3) daily mushroom powder consumption will lead to favorable changes in inflammatory marker of aging that correlate with the increase in bioactive compounds from mushrooms; (4) daily mushroom powder consumption will lead to changes in DNA methylation profiles.

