The level of inflammatory biomarkers and NfL in the blood will be assessed using an ELISA assays as previously described(Cheah et al., 2017). We decided to measure pro-inflammatory cytokines because both inflammatory damage has been well documented in both AD pathophysiology and the biology of aging(Querfurth and LaFerla, 2010) and the biology of aging(Franceschi et al., 2018). NfL levels have been suggested as a blood-based biomarker for neurological diseases (Fan et al., 2023). The level in plasma increases in preclinical Alzheimer’s disease (AD) before symptoms appear (Preische et al., 2019) and correlate with MCI and other AD hallmarks, such as brain shrinkage and tau tangles observed on PET scans (Raket et al., 2020). Here, we will use plasma NfL as a systemic biomarker for cognitive decline. We will generate epigenome-wide methylation data using the state-of-the-art Illumina Infinium MethylationEPIC BeadChip (Pidsley et al., 2016) on the HiScan system. The array covers over 850,000 methylation sites per sample at single-CpG site resolution, and provides unparalleled coverage of CpG islands, RefSeq genes, ENCODE open chromatin, ENCODE transcription factor binding sites, and FANTOM5 enhancers, as well as regions identified by the ENCODE project as potential enhancers. This epigenome approach will help shed light on unknown pathways and is superior to traditional approaches that focus on a limited number of genes. We will calculate epigenetic clocks using established methods and use these clocks as a quantitative measure of biological age compared with chronological age.

Furthermore, we will measure plasma ergothioneine levels using liquid chromatography-mass spectrometry at baseline, 12 months and 24 months. Correlating changes in blood ergothioneine levels with cognitive outcomes and with pathological and aging-related biological markers will shed light on ergothioneine’s mediating role in the hypothesized relationship between mushroom consumption and cognitive aging. The inclusion of biomarkers of both a mushroom-derived compound and of aging and dementia represents a novel approach not previously adopted in human studies.

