To examine the underlying protective mechanisms: The levels of biomarkers will be treated as continuous variables. Changes in biomarkers will be calculated by comparing post-intervention levels to pre-intervention levels from intervention and control and represented in percentage (%). These changes will then be compared between the intervention and control groups. Furthermore, paired two-tailed t-tests will be performed to assess whether biomarker levels differ between pre-intervention and post-intervention measurements within each group (control and intervention). To analyze the ergothioneine data, we will use a “change-versus-change’ approach, using repeated ergothioneine measurements as predictors to examine their relationship with changes in cognition and other biomarkers. We will further employ Structural Equation Modeling (SEM) to assess how the intervention affects cognitive function, with ergothioneine as a hypothesized mediating factor. In the SEM, we will adjust for age, sex, education (social class proxy), BMI, APOE ε4 status, baseline supplement use (curcumin, Ginkgo, omega-3), individual metabolic variations by including plasma liver enzymes (ALT, AST) and baseline renal function & ergothioneine levels as covariates, and compliance rate. Interaction terms will test effect modification.

To examine the epigenetic changes associated with ET-Rich mushroom consumption: Analysis of epigenome-wide methylation data will be performed using a modified version of the CPACOR pipeline(Lehne et al., 2015). Briefly, we will normalize marker intensities by quantile normalization. Single-marker tests using logistic regression will be used to examine the association of mushroom consumption with each autosomal CpG site (yes/no), adjusted for age and sex. Principal components from intensity values of Infinium control probes will also be included as covariates in the regression models. Finally, the association results will be adjusted for the genomic control inflation factor. We will subsequently develop a methylation risk score (MRS) model by taking a weighted approach (by effect size) for the CpG loci identified to be associated with mushroom consumption. Figure 3 describes the flow of study participants.

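### Blood biomarkers are compared between arms as percentage change with no baseline covariate, and the methylation model names neither baseline methylation nor change, so precision and interpretability are lost

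*Protocol article*

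**What the plan says.** All analysis statements are in section 3.5 (Methods of analysis) of the protocol article.

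- **Metric:** "Changes in biomarkers will be calculated by comparing post-intervention levels to pre-intervention levels from intervention and control and represented in percentage".
- **Between-arm comparison:** "These changes will then be compared between the intervention and control groups". Neither the test nor a baseline covariate is named. Baseline ergothioneine appears as a covariate only in the structural equation model for cognition.
- **Within-arm tests, added after that comparison:** "paired two-tailed t-tests will be performed to assess whether biomarker levels differ between pre-intervention and post-intervention measurements within each group".
- **Methylation:** "Single-marker tests using logistic regression will be used to examine the association of mushroom consumption with each autosomal CpG site (yes/no". The covariates named are age, sex and control-probe principal components, and a genomic control adjustment follows.

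Section 2 sets the methylation aim (Aim 4) as to "explore epigenome-wide DNA methylation changes following mushroom powder intervention" and to see whether such changes correlate with cognitive and biomarker outcomes. Section 3.4 and Table 1 place blood sampling at baseline and 24 months, so each participant's own baseline value is planned. Section 3.4 lists inflammatory markers, NfL, plasma ergothioneine and epigenetic age as secondary endpoints.

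**The concern.** Three stated choices use the baseline sample poorly or not at all.

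1. **Percentage change.** It divides by the baseline value, so in a right-skewed marker participants with low baselines dominate the arm mean. It also carries the full noise of the baseline measurement into the outcome, whereas covariate adjustment would remove noise.
2. **Within-arm paired tests.** They ask whether an arm moved over 24 months. Ageing, assay drift and regression to the mean can all cause that without any effect of the powder.
3. **The methylation model.** The aim is change after the intervention, but the model contains neither baseline methylation nor change. Its exposure is called consumption rather than randomised arm. That is ambiguous in a programme that also holds an observational cohort with measured diet and methylation.

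At stake are the precision and readability of the mechanism results (Aims 3 and 4).

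**Working it through.** **The plan's own figure.** The article sizes only the MMSE endpoint: d = 0.30, two-sided alpha 0.05, 90% power, 235 per arm, 300 enrolled. The normal approximation gives 234 and the noncentral t gives 234.5, rounded up to 235. Then 235/(1 − 0.20) = 294, close to 300. It reproduces and is not affected here. No power is stated for biomarkers.

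**Inputs.**
- From the article: 300 per arm and 20% attrition, so 300 × 0.80 = 240 evaluable per arm.
- Assumed, because the article gives none: lognormal marker; log-SD 0.8 (range 0.6–1.0); pre-post correlation r = 0.6 (range 0.5–0.7); true ratio 0.85, so the log effect is |ln 0.85| = 0.1625.

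**Base case on the log scale.** Power ≈ Φ(0.1625/SE − 1.96).
- ANCOVA: SE = 0.8 × √((1 − 0.36) × 2/240) = 0.0584; 0.1625/0.0584 = 2.78; power 79%.
- Log change, unadjusted: SE = 0.8 × √(2 × (1 − 0.6) × 2/240) = 0.0653; ratio 2.49; power 70%.
- 24-month value only: SE = 0.8 × √(2/240) = 0.0730; ratio 2.23; power 60%.

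**Percentage change (simulation, same inputs).** Power is about 59% with a t-test and 69% with a rank test. With the t-test, percentage change does about as well as ignoring baseline altogether.

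**Range of assumptions.**

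| log-SD | r | t-test on % change | log-scale ANCOVA |
|---|---|---|---|
| 1.0 | 0.5 | about 29% | about 53% |
| 0.8 | 0.6 | about 59% | about 79% |
| 0.6 | 0.7 | about 95% | about 98% |

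**Type I error.** With no effect, simulated rejection rates for the between-arm percentage-change test were 4–6%, so that comparison is valid.

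**Arm-level display.** If nothing changes, the log ratio has mean 0 and variance 2·SD²·(1 − r). Mean percentage change is therefore 100 × (exp(SD²(1 − r)) − 1):
- SD 0.6, r 0.7: exp(0.108) − 1 = +11%
- SD 0.8, r 0.6: exp(0.256) − 1 = +29%
- SD 1.0, r 0.5: exp(0.5) − 1 = +65%

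Both arms shift alike, so the arm difference is not biased. The figure shown for each arm is.

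**Within-arm tests.** Suppose a drift shared by both arms gives each paired test power p, with no effect of the powder. The chance that only the active arm is significant is p(1 − p): 0.5 × 0.5 = 25%, and 0.25 × 0.75 = 19%.

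**Methylation.** Aim 4 asks about change, and two samples per participant are planned, but the model's named terms are CpG, age, sex and control-probe components. If the term is the 24-month level and consumption means randomised arm, omitting baseline multiplies the variance of the contrast by 1/(1 − r²): 1.33 at r = 0.5, 1.56 at 0.6 and 1.96 at 0.7. These correlations are assumed and will differ by site.

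**The case against.** The strongest defence is that the plan does contain the randomised contrast. A reader might infer that the paired t-tests replace it. They do not: the sentence just before them compares the changes between arms, and the t-tests are additional. Nor does the article say that an effect will be claimed from significance in one arm only, so the 25% above shows what such a reading would cost and does not describe a stated plan.

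Other stronger readings also fail:

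- **That the percentage-change comparison is biased.** The upward shift is common to both arms and cancels, and type I error holds.
- **That the loss is 59% against 79% whatever the test.** The article does not name the test. A rank test recovers about half of the gap (69%).
- **That the methylation analysis is invalid.** If the yes/no term is the randomised arm, a follow-up-only comparison still tests the intervention, because randomisation balances baseline in expectation. The article also does not say outright whether a level or a change enters.
- **That a very large number of CpGs will be false positives.** "The array covers over 850,000 methylation sites per sample", but nowhere does the article test CpGs at a nominal 0.05, and it does not offer genomic control as multiplicity control. The pipeline is described in brief, and the threshold can sit in the SAP.
- **That the methylation risk score should be checked in DaHA.** That cohort would test dietary intake, a different exposure from the capsule.

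The endpoints concerned are secondary, and the methylation work is exploratory. What stands is that the metric, the within-arm tests and the methylation covariates are written down, and a more precise analysis of the same samples is available.

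**Conclusion.** The point holds as a matter of efficiency and clarity, not of bias in the arm comparison. Percentage change without baseline adjustment costs about 20 percentage points of power in the base case with a t-test (59% against 79%) and about 10 with a rank test (69% against 79%). Over the assumed range the t-test gives about 29%–95% against 53%–98%. These sizes rest on an assumed lognormal shape, log-SD, correlation and a 15% reduction, none of which the article gives. ANCOVA was ahead in every setting tried. Arm-level percentage changes of +11% to +65% with no true change would mislead a reader, and the paired tests do not test the intervention. The methylation model as worded does not match Aim 4 and leaves the baseline sample unused. The primary MMSE analysis is unaffected. This is a free improvement.

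**What to change.** Amend section 3.5 or fix the following in the SAP before unblinding:

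1. **Blood biomarkers.** Make the main analysis the 24-month log level (epigenetic age in years) regressed on randomised arm, adjusted for its own baseline, age and sex. Report ratios of geometric means for the log-scale markers.
2. **Plasma ergothioneine.** Keep the 12-month measurement in a repeated-measures version of the same model. Section 3.4 plans that measurement, while Table 1 shows no 1-year blood sample, so the two should be reconciled first.
3. **Within-arm changes.** Show them descriptively only and drop the paired t-tests as inference.
4. **Each CpG.** Model the 24-month M-value on randomised arm, with baseline M-value, age, sex and control-probe components as covariates. Replace the word consumption with randomised arm.

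The cost is wording. The baseline and 24-month samples are already planned, and no extra participants or visits follow from the change of model.

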Maintaining cognitive function with advancing age is an important and challenging question that requires well-founded research with good translational opportunities. This is particularly important for at-risk populations such as Apolipoprotein E (*APOE*) ε4 allele carriers (Harris, 2024), those with a family history of dementia (Lee et al., 2022), and those at an early stage of cognitive decline, known as Subjective Cognitive Decline (SCD) (Jessen et al., 2014). Without early intervention, these at-risk populations groups are likely to progress to dementia. Prevention should be the focus at population level because current anti-dementia therapies only delay the progression of the disease. For example, the latest approved antibody intravenous (IV) infusion therapy, Lecanemab, only showed a moderately lesser decline in measures of cognition and function than placebo and it was associated with adverse events (van Dyck et al., 2023). Epidemiological studies have reported that higher mushroom consumption is associated with better cognitive performance—across word recall, executive function, and prospective memory—and with lower risk of incident dementia (Cha et al., 2024; Ba et al., 2022; Aoki et al., 2024). Mushrooms contain bioactive compounds such as ergothioneine, which has antioxidant and anti-inflammatory activity and has demonstrated neuroprotective effects in cell and animal models, but human evidence for a definitive neuroprotective effect remains limited. In a recent double-blind, placebo-controlled pilot trial, 14 older adults with MCI received ergothioneine supplementation (25 mg per capsule, thrice weekly) for one year. The intervention was well tolerated, and the ergothioneine group showed modest improvements on the Rey Auditory Verbal Learning Test, as well as stabilization of plasma neurofilament light chain levels—findings that suggest a potential slowing of neuronal damage but require confirmation in larger trials (Yau et al., 2024).

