
**Table 1 tab1:** Measurements and visit schedules.

S.no.	Measurement	Baseline	1 year	2 years
1	Socio-demographics	√		√
2	Lifestyles, dietary intake (FFQ)	√	√	√
3	Medical conditions, medications, supplements	√	√	√
4	Mini mental state examination (MMSE)	√	√	√
5	GDS-15 or PHQ-9 for depressive symptoms	√	√	√
6	Neuropsychological tests (3 cognitive tests as a battery)	√	√	√
7	Clinical dementia rating (CDR)	√	√	√
8	Handgrip strength, repeated chair rise test, blood pressure	√	√	√
9	Venous blood sample collection and blood-based biomarkers	√		√

For cognitive measures, we selected locally validated and normed tools to ensure sensitivity to changes over time. We have carefully considered and included a panel of biological markers based on potential pathways. We will measure pro-inflammatory cytokines (such as hs-CRP, TNFα, IL-1, IL-6, etc.), and neurofilament light chain (NfL) as a non-specific biomarker of neurodegeneration (AD). We will also measure the genetic polymorphism of *APOE* gene and the DNA methylation profile. This biological approach has a clear advantage over traditional trials that only assess clinical outcomes and clinical laboratory tests.

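### The mediation SEM omits the baseline cognitive score, so its ergothioneine-to-cognition path loses precision and stays open to confounding by starting cognition

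*Protocol article*

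**What the plan says.** Section 3.5 (Methods of analysis) plans an SEM "to assess how the intervention affects cognitive function, with ergothioneine as a hypothesized mediating factor". It then lists the adjustment variables. The first part reads "In the SEM, we will adjust for age, sex, education (social class proxy), BMI, APOE ε4 status, baseline supplement use (curcumin, Ginkgo, omega-3"), and the list ends with "plasma liver enzymes (ALT, AST) and baseline renal function & ergothioneine levels as covariates, and compliance rate".

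The list therefore holds the starting value of the mediator and a measure of capsule-taking, but no starting value of MMSE, SDMT, CTT or RAVLT. These are available: Table 1 in section 3.4 schedules the MMSE and "Neuropsychological tests (3 cognitive tests as a battery") at baseline, 1 year and 2 years. Nothing elsewhere in the article adds a baseline cognitive score to the SEM. The MMSE split at 27 in section 3.5 defines subgroups and is not a covariate.

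The article does not say whether the SEM outcome is the 24-month score or the change. The analysis described just before it works with change, "using repeated ergothioneine measurements as predictors to examine their relationship with changes in cognition and other biomarkers".

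**The concern.** Randomisation protects two effects: arm on ergothioneine, and arm on cognition. It does not protect the third link, ergothioneine on cognition, because participants are not randomised to the ergothioneine level they reach. Any common cause of follow-up ergothioneine and follow-up cognition that is left out can distort that link.

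Starting cognition is a natural candidate. It predicts later cognition, and the Introduction reports from cohort studies that "higher mushroom consumption is associated with better cognitive performance", mushrooms being a dietary source of ergothioneine. Section 3.4 relies on the ergothioneine analyses to shed light on its mediating role, and aim 3 is the mechanism aim. At stake is how far the mediated effect can be believed, and how precisely it is estimated.

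**Working it through.** **The plan's own figure.** The article gives no calculation for the SEM, only for the primary endpoint: d = 0.30, two-sided 5%, 90% power, 235 per arm. With the normal approximation, n = 2 × (1.960 + 1.282)² / 0.30² = 233.5, so 234; the t-test solution is 234.5, so 235. Allowing 20% attrition, 235 / 0.80 = 294, and 300 are planned. The figure reproduces and is not at issue. The number analysed below is 600 × 0.80 = 480.

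**Inputs not in the documents (assumptions).**
- ρ, the correlation of baseline with 24-month cognition: 0.6, with a range of 0.3 to 0.8.
- Variance of follow-up ergothioneine given arm and baseline ergothioneine: 0.75.
- True path: 0.15 or 0.10 SD of cognition per SD of ergothioneine.

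**Precision, with no confounding assumed.** In SD units the residual variance of the cognition equation is:
- with the baseline score: 1 − ρ²
- change, no baseline score: 2(1 − ρ)
- 24-month score, no baseline score: 1

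Ratio of the standard error with the baseline score to that without it:

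| ρ | against change | against 24-month score |
|---|---|---|
| 0.3 | 0.81 | 0.95 |
| 0.5 | 0.87 | 0.87 |
| 0.6 | 0.89 | 0.80 |
| 0.7 | 0.92 | 0.71 |
| 0.8 | 0.95 | 0.60 |

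The standard error therefore falls by 5% to 19% against change, and by 5% to 40% against the raw score.

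**Power at ρ = 0.6.** SE = √(residual variance / (480 × 0.75)) = √(residual variance / 360), and power ≈ Φ(path / SE − 1.96).

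| Model | Residual variance | SE | Power at 0.15 | Power at 0.10 |
|---|---|---|---|---|
| Change, no baseline | 0.80 | 0.0471 | 89% | 56% |
| 24-month score, no baseline | 1.00 | 0.0527 | 81% | 47% |
| Baseline included | 0.64 | 0.0422 | 94% | 66% |

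Simulated trials agree. Without the baseline score, power is 88% to 90% and 57% to 58% for change, and 79% to 81% and 48% for the raw score. With it, power is 93% to 94% and 65% to 66%.

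**Confounding: direction only.** Let δ be the slope of baseline cognition on follow-up ergothioneine, given arm and the listed covariates. Leaving out the baseline score shifts the path by ρδ when the outcome is the 24-month score, and by (ρ − 1)δ when it is change. At ρ = 0.6 these are +0.6δ and −0.4δ. Using change does not remove the bias; it reverses its sign. If δ = 0 there is none. The documents give no information on δ.

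**Does the listed compliance rate already deal with it?** Trials were simulated with 480 participants, a true path of zero and an assumed cognition-compliance correlation of 0.3. Baseline cognition acted on ergothioneine only through compliance, so that 1 SD went with 0.1 to 0.3 SD more rise. Leaving out both compliance and baseline cognition gave rejection rates of 11% to 40% (score) or 8% to 25% (change) at a nominal 5%. Adding compliance alone brought them to 4% to 5% if it is measured without error, and to about 5% to 7% at a reliability of 0.6. The existing list therefore largely closes that route.

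**The case against.** A reader might infer that the SEM, as listed, will often report mediation that is not there. The documents do not support this. High false-positive rates arise only if compliance is left out of the model, which the plan does not do ("baseline renal function & ergothioneine levels as covariates, and compliance rate"), or if baseline cognition is assumed to act on ergothioneine by some further route. The obvious behavioural route is how reliably capsules are taken, and compliance covers most of it; the Discussion also plans to cross-check the diary against electronic pill caps. The dietary route runs partly through baseline ergothioneine, which is listed, and is narrowed by the entry limit of mushrooms no more than once a week. The cited cohort associations do not show that starting cognition predicts a capsule-driven rise in ergothioneine among participants who all have CDR 0. All of this stands, so the path can be called open to confounding but not shown to be confounded.

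Two further arguments carry less weight. The analysis is secondary, and the Introduction says the mechanisms are to be explored; that limits the consequence but does not justify giving up precision. It may also be said that a full analysis plan could place baseline cognition in the model structure and not in the covariate list. That is possible. However, the article lists the mediator's own baseline among the covariates and goes into such detail as liver enzymes, so the natural reading is that the outcome's baseline is not included.

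It is fair to add that the article leans towards change scores, so the smaller precision gain is the more relevant one.

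**Conclusion.** The point holds as a worthwhile improvement to a stated model. Two things follow from the omission.

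First, precision is lost for any plausible ρ. At ρ = 0.6 with 480 analysed, the loss against a change outcome is about 6 points of power for a path of 0.15 (about 88% against 94%) and about 8 points for 0.10 (about 58% against 66%). It is larger if the outcome is the raw 24-month score. The correlation, the ergothioneine variance and the path sizes are assumptions.

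Second, the ergothioneine-to-cognition path remains open to confounding by starting cognition through routes that compliance, baseline ergothioneine, age and education do not capture. Diet during follow-up that a single baseline ergothioneine value misses is one example. The size cannot be derived from the documents, and the sign would depend on whether the outcome is score or change.

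The primary comparison, the total effect of the intervention and the sample size are unaffected.

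**What to change.** In section 3.5, put the baseline score of the cognitive test being analysed at the head of the SEM covariate list, and state that it enters both the equation for follow-up ergothioneine and the equation for follow-up cognition. Also state whether the outcome is the 24-month score or the change, and keep the baseline score in either way. With it in, both forms give the same ergothioneine coefficient, because subtracting the baseline only lowers the coefficient of the baseline score by 1.

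The cost is one covariate and one degree of freedom per equation. The score is already scheduled at baseline, so only the analysis wording changes. If the full analysis plan already includes it, one added phrase in the article's list settles the matter.
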